## Abstract

**Background:**

Studies have shown that excessive screen time exposure and a lack of physical exercise are associated with nonspecific back pain in adolescents. Reduced screen time exposure and Surya Namaskars (Sun Salutations) have physical and psychological benefits. We aim to test a novel comprehensive school-based intervention module—Screen time reduction and Surya Namaskars (SanSKAR) for reducing the proportion of school-going adolescents reporting nonspecific back pain. The word “sanskar” originates in Sanskrit and roughly means good values or actions.

**Methods:**

The study will be conducted in one of the six geographic divisions of a state in western India. 540 adolescent students from randomly selected urban and rural schools across five districts of this division will be included after informed assent and parental consent. Students’ heights, weights, school bag weights, and the presence and characteristics of back pain will be recorded with an on-site clinical examination by a pediatric orthopedic surgeon to rule out specific causes. Those with nonspecific back pain will perform SanSKAR: at least 12 Surya Namaskars daily at least five days a week for 16 weeks with screen time exposure of not more than 60 min per day. Post-intervention outcomes (proportion of students with back pain and its severity) will be measured at 8 weeks and 16 weeks.

**Discussion:**

This study will help test a novel multipronged school-based intervention for back pain in adolescents. The results could inform practice changes for nonspecific back pain in school-going adolescents.

**Clinical Trial Registration:**

identifier (CTRI/2024/07/070522).

## Introduction

Back pain poses an important public health challenge in today's world, not only in adults but also in children, leading to loss of academic hours, as well as personal impacts. The prevalence of back pain in children is found to be variable, with a lifetime prevalence ranging from 5% to as high as 75% (1, 2). Childhood back pain is believed to be more prevalent than previously thought, and the burden approaches that found in adults (2). Back pain in childhood predisposes the individual to the chronicity of back pain in adult life, too (3–5). Based on published literature and our own previous work in this field, back pain in the school-going adolescent age group is found to be associated with physical factors such as back injury (6), mode of transport to school, lack of engagement in sports (7), and the type and weight of the school bag, and method of carrying the school bag. Several other factors have been found to be associated with back pain, such as age, sex and BMI of the adolescent, type of school furniture and its ergonomics. Psychosocial factors such as emotional, conduct, hyperactivity, and peer problems have been found to be associated with back pain, as has the presence of a family member complaining of back pain (3, 4, 7). Screen time exposure (mobile phones, television, and laptops) is another significant contributory factor (8, 9). In India, the entire focus of all the published studies so far, except one (7), has been on the “weight of the school bag” (10–19), while others have considered postural changes associated with school bag weight (15, 20, 21). Also, in India, almost all the work in this area has been done in urban schools. There is only one study from Bhubaneshwar (22) which has included rural school-going children.

Engel's biopsychosocial model projects back pain as a complex interplay of various social, psychological, and biological factors (23, 24). The Ministry of Health and Family Welfare, Government of India, has issued operational guidelines regarding the school health program under Ayushman Bharat. They recommend “the promotion of Yoga and meditation” by incorporating the same in middle and high school curricula with a focus on “special attention to the physical, psychosocial and mental aspects” of child development (25). However, as published in a review in 2023, numerous gaps in the implementation of the holistic Ayushman Bharat school health guidelines have been discussed (26). Surya Namaskars (SN) (Figure 1) are a series of successively and continuously performed sets of 12 postures or asanas (also described as Sun Salutations) and are a component of Hatha Yoga.

**Figure 1 F1:**
[figure not shown]
The twelve Surya Namaskar poses.

SNs have been proven to enhance cardiorespiratory fitness levels, “promote weight management” (27), and be a better alternative to aerobic exercise when compared with endurance training on a stationary bicycle (28). The effect of SNs on the involved muscles using electromyography (29) has shown that SNs improve the mobility of almost all the joints of the body, with “high-to-moderate activation” of all the major truncal and lower limb muscles, concluding that SNs can be safely prescribed for not only the management but also the prevention of mechanical back pain. SNs have been shown to result in psychological benefits such as reduction in stress, anxiety, and depression, as well as improvements in emotional intelligence and quality of life in adults as well as children and adolescents (30–37).

Interventions to reduce screen time in adolescents have involved parental participation through interactive group sessions, informative flyers, posters, reminders, and maintenance of log books (38, 39). Since back pain in children is a complex conglomeration of various physical and psychosocial factors, an ideal intervention would need to be tailored to address both.

There is sufficient evidence in the currently available scientific literature to hypothesize that a structured intervention tailor-made for implementation in the school environment that includes performing Surya Namaskars and limiting screen time exposure with parent and teacher engagement could be beneficial in reducing the prevalence and intensity of non-specific back pain in adolescents. Such an intervention needs to be feasible for execution in the school environment, requiring minimal resources, and garnering student, teacher, and parent engagement so that the shared responsibility makes it more acceptable and practical.

The objectives of this study are to test a novel comprehensive intervention module “SanSKAR” (Screen time reduction and Surya Namaskars for 16 weeks) for reducing the proportion of school-going adolescents aged 10–16 years reporting moderate-to-severe back pain as well as the overall proportion of students with back pain.

## Methods and analysis

From our previous study, the proportion of students reporting moderate-to-severe back pain as measured on a VAS scale was 71.6% (7). Assuming that the intervention will cause a 15% reduction in this proportion with a 95% confidence interval and 90% power, assuming a 20% dropout rate, the calculated sample size is 270 students. To ensure sound representativeness of the results and considering the plan to conduct various sub-group analyses, this sample size will be doubled to include 540 students.

Our sampling frame will be urban and rural schools located in each of the five districts of Pune Division, namely Pune, Satara, Sangli, Kolhapur, and Solapur (Figure 2).

**Figure 2 F2:**
[figure not shown]
Pune division, maharashtra state (area of study marked in the black triangle).

Random numbers will be generated using Microsoft Excel against the lists of urban and rural schools. These numbers will be arranged in ascending order, and the first school from each pool will be approached for permission to conduct the study. If permission is refused, the next school on the list will be approached. Schools will be enrolled till the desired sample size is met. The respective school Principals will be approached for permission to conduct the study. Girls and boys studying in standards 5, 7, and 9 (who are typically between ages 10 and 16 years in Indian schools) will be enrolled as representatives of the adolescent age group if they provide written assent and parental written informed consent. Students younger than 10 years will be excluded.

This is a before-and-after study to be carried out in three phases. Phase I, where the baseline pre-intervention data will be collected; Phase II, where the intervention (SanSKAR) will be carried out on students reporting back pain; and Phase III, where the post-intervention data will be collected at the end of 8 and 16 weeks.

### Phase I

#### First visit

During the first school visit, child assent forms, parental consent forms, and printed information sheets detailing the study procedures will be distributed in the classes and sent home with the students. The project details will be discussed in detail with the respective class teachers and physical education teachers. After allowing a period of 8–10 days for responses, the date for the baseline data collection will be fixed.

#### Second visit

All the study-related procedures will be explained to the students, including height and weight measurement, school bag weight measurement, and guidelines for answering the questionnaires. A proforma will be used to document the age, sex, school grade, school bag weight, type of school bag, and students' heights and weights. A month's recall of back pain will be documented. The proforma will also include a diagram for marking the location of back pain and a visual analog scale (VAS) to note the pain severity. Details of back pain, such as frequency, duration of an episode, treatment sought, absence from school, aggravating factors, and perceived reasons, will be documented. Students will be asked to document a week's recall of the average daily time spent on mobile phones, laptops, and televisions.

Psychological data will be recorded using the self-administered Strengths and Difficulties Questionnaire (SDQ) (40) to assess prosocial behavior (strength) and hyperactivity, emotional problems, peer problems, and conduct problems (difficulties). A pediatric orthopedic surgeon will conduct an on-site clinical examination of students with back pain to identify specific causes, if any. A scoliometer examination will be performed with the student stooping forward. The scoliometer that will be used is a standard instrument developed by [name], MD (US Patent number 5181525). It is a small hand-held device used for measuirng the angle of trunk rotation (ATR). It has a notched edge and a bubble to indicate the ATR. A straight leg raise test to look for nerve root tension signs and the flexion-abduction-external rotation test to evaluate the sacroiliac joint will be done. Based on history and physical examination, imaging will be suggested if there is clinical suspicion of a specific cause of back pain. Data from Phase I will be analyzed to determine the proportion of students with back pain, its characteristics (location, intensity, frequency), and the associated physical and psychosocial factors. The SDQ scores will be computed as specified in the standard key and students will be categorized as those with low needs and those with some/high needs across the various domains.

### Phase II

#### The intervention

SanSKAR (**S**creen time reduction **an**d Surya Namas**kar**s) for students reporting back pain in Phase I.

Screen time reduction: The researcher will counsel class teachers and parents using a PowerPoint presentation and handouts detailing the intervention, including SNs and screen time reduction to not more than 60 min per day across all devices such as mobile phones, computers, laptops, tablets, and television. The counseling will include evidence-based recommendations on age-appropriate screen time exposure (41). This will be reinforced at teacher and parent engagements in weekly or fortnightly (as possible) meetings for repeated and regular advocacy and monitoring. Weekly reminders about limiting screen time exposure will be sent to the parents through the official school communication channel. The parents will be handed out a daily diary to record their child's daily screen time usage. In addition, parents will be urged to enforce a complete restriction on their child's involvement in heavy domestic or farm work (as applicable, depending upon the urban or rural setting).

#### Surya namaskars

The routine will consist of 5 min of warm-up exercises, 12 SNs with a maximum duration of 1.5 min/SN followed by *Shavasana* for a maximum of 5 min for at least 5 days a week to be continued for 16 weeks. The session is expected to last for a maximum of 30 min. Students will start the routine at least an hour after food intake, preferably in the morning. Training will be imparted to the students along with the respective class teachers and physical education instructors. Monitoring for the correctness of the technique of SNs will be continued for 5 days. Regular follow-up and monitoring of the implementation of the intervention will be done during planned school visits (minimum 8 visits and maximum 16 visits as may be practically possible) in addition to the daily monitoring by the class teachers/physical education instructors in the school.

### Phase III

Data collection will be done at the end of the 8th and 16th weeks for outcomes of interest such as the proportion of students reporting back pain, the intensity of back pain, and SDQ scores. The frequency and number of SNs performed will be noted as well as daily screen time durations. Associations if any between back pain and the physical and psychosocial factors will be determined using appropriate statistical tests. Differences in the pre- and post-intervention phases will be reported.

## Data analysis

Data will be entered in Microsoft Excel and then imported to SPSS (version 25) for Windows package (IBM SPSS Statistics for Windows, Version 25.0. Armonk, NY: IBM Corp). The associations between qualitative and quantitative variables will be determined using the chi-square test. Odds ratios will be obtained for each predictor. Multivariate regression analysis will be carried out to determine predictors of outcome variables. Pre- and post-intervention variables of interest will be analyzed by comparing their means using the paired *t*-test or comparing proportions using the McNemar test.

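### The chi-square test is named for associations between qualitative and quantitative variables, which it can assess only after the quantity is cut into classes

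*Protocol article*

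**What the plan says.** The Data analysis section assigns one bivariate test to mixed pairs of variables: "The associations between qualitative and quantitative variables will be determined using the chi-square test". It then plans an odds ratio for each predictor, followed by a regression: "Multivariate regression analysis will be carried out to determine predictors of outcome variables". The paired t-test and McNemar's test are named only for comparing values before and after the intervention. No t-test, Mann-Whitney test, analysis of variance or correlation is named for the associations.

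The candidate factors are set out under Second visit (Phase I). "A proforma will be used to document the age, sex, school grade, school bag weight, type of school bag, and students' heights and weights". Students also report "a week's recall of the average daily time spent on mobile phones, laptops, and televisions", and the form has "a visual analog scale (VAS) to note the pain severity". Age, bag weight, height, weight, screen time and pain severity are all quantities. BMI is not listed as recorded. It can be derived from height and weight, and the Introduction names it among associated factors ("age, sex and BMI of the adolescent, type of school furniture and its ergonomics").

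Phase III describes the association analysis without naming a test: "Associations if any between back pain and the physical and psychosocial factors will be determined using appropriate statistical tests".

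**The concern.** A chi-square test of association works on a table of counts, so both variables must be categorical. A qualitative variable against a quantity is a different problem, and the plan's sentence gives that problem to the wrong test. An analyst who follows it literally has to group bag weight, screen minutes or age before testing.

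Two things are then at stake. Grouping throws away the ordering and spacing of values within each class, so a real association is harder to detect. The result also depends on where the cut falls, so a factor can look associated with back pain at one threshold and not at another. Finding the physical and psychosocial factors associated with back pain is a stated purpose of the Phase I analysis, and screen time is both a candidate factor and a target of the intervention.

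**Working it through.** **The plan's own figure, to see whether this point touches it.** Methods and analysis gives 71.6% with moderate-to-severe pain, a 15% reduction, 95% confidence, 90% power, 20% dropout and a result of 270. Read the reduction as 15 percentage points (71.6% to 56.6%), two-sided, and use McNemar's formula with independent before and after responses:

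- Discordant cells: 0.716 × 0.434 = 0.3107 and 0.284 × 0.566 = 0.1607, sum 0.4715.
- n = (1.960 × √0.4715 + 1.2816 × √(0.4715 − 0.0225))² / 0.15² = (1.3458 + 0.8587)² / 0.0225 = 216.
- With dropout: 216 / 0.80 = 270.

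The two-proportion formula gives 213, and 213 / 0.80 = 267 after rounding up. The 270 therefore reproduces, and so does the 540 obtained by doubling it. Neither uses the association test, so this point leaves both alone.

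**Does the named test fit the variable types?** Back pain yes/no is qualitative. Age, bag weight, height, weight and screen time are recorded as quantities. The chi-square test needs classes on both sides, so the named test does not fit the pair it is named for. This step needs no numerical assumption.

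**What would cutting cost? (illustration)** Assume a normally distributed predictor, a small (local) effect and a cut into two groups with share q above the cut c. Relative to the continuous analysis, the efficiency is φ(c)² / [q(1 − q)], where φ is the standard normal density. For a median split, c = 0 and φ(0)² = 1/(2π) = 0.159, so the efficiency is 0.159 / 0.25 = 2/π = 0.637.

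The last column takes a continuous analysis with 80% power and gives Φ[(1.960 + 0.8416) × √efficiency − 1.960]. For the median split that is Φ(2.8016 × 0.798 − 1.960) = Φ(0.275) = 0.608.

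| Share above the cut | Relative efficiency | Power, if 80% when continuous |
|---|---|---|
| 50% | 0.64 | 61% |
| 30% | 0.58 | 57% |
| 20% | 0.49 | 50% |
| 10% | 0.34 | 37% |

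**Does the cut-point change the answer? (illustration)** A simulation took 540 students, assumed to be half with and half without back pain, and a normal predictor. The mean difference was 2.8016 × √(1/270 + 1/270) = 0.241 standard deviations, set to give the t-test 80% power. Over 4,000 data sets the t-test had 80% power. The chi-square test had 60%, 57%, 45% and 41% for the four cuts in the table. These depart somewhat from the formula at the uneven cuts, as can happen with a discrete table. In about 58% of data sets the four cuts did not agree on significance.

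**The case against.** The strongest reply is that the sentence is a drafting slip with little effect. Phase III promises suitable tests, and the Data analysis section goes on to odds ratios and a regression, both of which can take bag weight or screen minutes as continuous. Part of that stands: the plan leaves room for a sound analysis, and the loss may never arise. It does not clear the sentence. The Data analysis section is where the test is specified, and it names an unsuitable one. A slip in the published plan still needs correcting.

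Several stronger readings are tempting, and the documents do not support them:

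- *That the regression is built on the chi-square results.* The article lists the methods side by side. It does not say that bivariate results select the predictors.
- *That the missing cut-points are a defect.* A condensed article commonly leaves such detail to the full protocol or analysis plan, so their absence is no finding. The misassigned test is.
- *That the plan throws away the SDQ scores.* It does state that "students will be categorized as those with low needs and those with some/high needs across the various domains", but the scores are computed by the standard key, and Phase III lists them as outcomes. Using them as continuous predictors is a modelling choice.
- *That the study in effect shrinks from 540 to about 344 students* (540 × 0.637). The article gives no distribution for any factor and plans no median split. It also sets no power target for the association analyses, so no planned power is lost. For pain severity, 540 would be the wrong base anyway, since severity is meaningful mainly among students with pain.

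**Conclusion.** The point holds as an error in what the plan states, limited to the secondary association analyses. The mismatch between test and variable type is certain from the text. Its numerical cost is not: 64% of the information kept, or less with uneven cuts, describes what two-group cutting does to a normal predictor under a small effect, not a measured property of this study. The loss would be smaller if the regression keeps factors continuous. The stated objectives, which are reductions in the proportions with moderate-to-severe and with any back pain, rest on before/after comparisons that this does not touch.

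**What to change.** Reword the sentence in the Data analysis section so that:

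- chi-square, or Fisher's exact test where cells are sparse, is used only for two categorical variables;
- quantitative factors (age, bag weight, height, weight or derived BMI, screen time) are related to back pain by logistic regression on the continuous value, with an odds ratio per stated unit, or compared by a t-test or Mann-Whitney test;
- the same factors stay continuous in the multivariable model.

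Entering continuous SDQ scores as predictors is optional. Clustering of students within schools is a separate question, and this change does not settle it. The cost is a change of wording: the data, SPSS and the sample size stay as they are.

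### The sample size and the pre-post tests take students as independent, although schools are sampled and school staff run the intervention; if change in pain varies by school, standard errors are too small

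*Protocol article*

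**What the plan says.** Under Methods and analysis, the sample size rests on a previous study in which "the proportion of students reporting moderate-to-severe back pain as measured on a VAS scale was 71.6" per cent. The article continues: "Assuming that the intervention will cause a 15% reduction in this proportion", "with a 95% confidence interval and 90% power", and then "assuming a 20% dropout rate, the calculated sample size is 270 students". The number is doubled to 540 for representativeness and subgroup analyses; clustering is not among the reasons.

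The sampling text below Figure 2 draws random numbers against lists of urban and rural schools and approaches schools in that order. It adds: "Schools will be enrolled till the desired sample size is met". Consenting students in standards 5, 7 and 9 are enrolled. The design is before-and-after, with no control group.

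Under Phase II, class teachers and physical education instructors are trained alongside the students and monitor the sessions daily. The research team makes between 8 and 16 visits, as practicable. Teachers are counselled together with parents, and reminders to parents go through the school's communication channel.

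Under Data analysis, pre- and post-intervention values are compared by the paired t-test for means or by "comparing proportions using the McNemar test". The article nowhere mentions clustering, an ICC, a design effect or a school term.

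**The concern.** Students in one school share the teachers who supervise the routine, the number of research visits, and the vigour with which the school follows the programme up. Their changes in pain may therefore resemble each other more than those of students from different schools. The paired t-test and the McNemar test remove what is stable within a student, but they then treat each student's change as a separate piece of information. If changes are correlated within school, the true variance of the mean change exceeds the variance these tests use.

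The comparison matters because it is the only test of effect in the study. With no control group, the claim that SanSKAR reduces back pain rests on it, and the article says that the results could inform practice. A standard error that is too small overstates that evidence.

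**Working it through.** **Step 1: reproduce the 270.** Inputs from Methods and analysis: 71.6% before; a 15% reduction, read as 15 percentage points, so 56.6% after; 95% confidence, read as two-sided 5%; 90% power; 20% dropout.

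McNemar formula, with before and after readings taken as independent:

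- discordant proportion: 0.716 × 0.434 + 0.566 × 0.284 = 0.3107 + 0.1607 = 0.4715
- difference d = 0.15, d² = 0.0225
- n = (1.960 × √0.4715 + 1.282 × √(0.4715 − 0.0225))² / 0.0225 = (1.346 + 0.859)² / 0.0225 = 216.0
- with dropout: 216.0 / 0.8 = 270.0

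The ordinary two-proportion formula gives 213, and 213/0.8 rounds up to 267. A relative reduction of 15% (71.6% to 60.9%) gives about 511 by the McNemar formula and does not fit. So 270 is a student-level number with nothing left over for clustering.

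**Step 2: allow for schools.** The article gives neither the ICC nor the number of schools. Assumptions: 10 schools (for example one urban and one rural in each of five districts) or 20 schools; equal numbers per school; ICC of 0.01, 0.02 or 0.05. ICC here always means that of the pre-post change, because stable differences between schools cancel in paired data.

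- design effect DE = 1 + (m − 1) × ICC, where m is the number of pairs per school
- effective n = pairs / DE
- power = Φ[(0.15 × √(effective n) − 1.960 × √0.4715) / √(0.4715 − 0.0225)]
- type I error of the unadjusted 5% test = 2 × [1 − Φ(1.960 / √DE)]

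Two numbers of pairs are shown: 216 (270 × 0.8) and 432 (540 × 0.8).

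| Pairs | Schools | m | ICC | DE | Effective n | Power | Type I error |
|---|---|---|---|---|---|---|---|
| 216 | 10 | 21.6 | 0.01 | 1.21 | 179 | 84% | 7% |
| 216 | 10 | 21.6 | 0.02 | 1.41 | 153 | 78% | 10% |
| 216 | 10 | 21.6 | 0.05 | 2.03 | 106 | 62% | 17% |
| 216 | 20 | 10.8 | 0.01 | 1.10 | 197 | 87% | 6% |
| 216 | 20 | 10.8 | 0.02 | 1.20 | 181 | 84% | 7% |
| 216 | 20 | 10.8 | 0.05 | 1.49 | 145 | 75% | 11% |
| 432 | 10 | 43.2 | 0.01 | 1.42 | 304 | 97% | 10% |
| 432 | 10 | 43.2 | 0.02 | 1.84 | 234 | 92% | 15% |
| 432 | 10 | 43.2 | 0.05 | 3.11 | 139 | 74% | 27% |
| 432 | 20 | 21.6 | 0.01 | 1.21 | 358 | 99% | 7% |
| 432 | 20 | 21.6 | 0.02 | 1.41 | 306 | 97% | 10% |
| 432 | 20 | 21.6 | 0.05 | 2.03 | 213 | 90% | 17% |

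The power column is for a test that holds its 5% level. It ignores the degrees of freedom lost with few schools, so it is slightly favourable.

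**Step 3: what the doubling does.** It can absorb a design effect of 432/216 = 2. With 432 pairs, power therefore stays at 90% or more up to an ICC of 1/(43.2 − 1) = 0.024 with 10 schools, or 1/(21.6 − 1) = 0.049 with 20. The error rate does not benefit. With 10 schools and an ICC of 0.02 it rises from 10% to 15% as the pairs double, because each school is larger. If the extra students come from extra schools (10 to 20, m unchanged at 21.6), it stays at 10%.

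**Step 4: how many pairs there will be.** The 540 are all enrolled students, but only those reporting back pain receive the intervention. If only they are analysed, there are fewer than 432 pairs. As an illustration, if half had pain, 540 × 0.5 × 0.8 = 216. The article does not give an expected proportion.

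**The case against.** The strongest reply is that no ICC is given and that the relevant one may be small. The pairing removes stable school differences, and the screen-time limit is carried out and recorded by parents at home. If change does not vary by school, the named tests are valid. This stands, and it is why every figure above is conditional. It does not remove the concern: the exercise component is supervised by each school's own staff, and the number of visits is allowed to vary, so an ICC of exactly zero is not a safe default.

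A second reply is that 540 students give ample power. That is right over part of the range: if all 540 count, power under independence is 99.6%, and it remains at 92% with 10 schools and an ICC of 0.02. A reader might infer that the stated 90% power is certainly missed; the article does not support that for the doubled sample. The reply does not touch the standard errors.

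Other stronger readings also go too far:

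- A reader might take the open-ended enrolment rule to mean that three or four large schools could fill the sample. The Abstract places the schools across five districts, which four schools cannot cover.
- A reader might say that whole schools are sampled. Only consenting students in three standards are enrolled.
- A reader might infer that the named tests lose any student who misses a visit. A comparison of baseline with week 16 keeps a student who missed only week 8.
- The multivariate regression is not specified, so a school term there is not excluded. The point concerns the pre-post tests, which are named.

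**Conclusion.** The point holds in conditional form. Schools are the sampling unit and school staff supervise the sessions, yet the 270 and the two named pre-post tests treat students as independent. If the ICC of the change is above zero, the unadjusted standard errors are too small by a factor of √DE, and the type I error exceeds 5%.

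Over an ICC of 0.01 to 0.05 and 10 or 20 schools, all assumed, the type I error is 6% to 17% with 216 pairs and 7% to 27% with 432. Power is 62% to 87% with 216 pairs and 74% to 99% with 432. The loss of power is thus uncertain for the planned 540 and depends on how many of them contribute pairs. The understated standard error follows from the named tests whenever change varies by school, whatever the sample size. This is not detail left to a fuller plan, because the article itself names the tests and the sample size inputs.

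**What to change.** In Data analysis, replace the unadjusted McNemar and paired t-tests for the pre-post comparisons by a GEE or mixed model, logistic for proportions and linear for means. It should account for repeated measures within student and for clustering by school, and use a small-sample correction because schools may be few.

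In Methods and analysis, state the expected number of schools and the number of students expected to contribute pairs. Restate power for that sample over a stated range of the ICC of the change, and say that the ICC is of the change and not of prevalence.

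The cost is wider confidence intervals, a less favourable stated power and a little more analysis work. The SPSS version that the article names has GEE and mixed-model procedures, and no new data are needed beyond a school identifier.

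### The named before-after tests use complete pairs only in a plan that expects 20% dropout, so the estimated fall in pain may be biased if dropout relates to outcome

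*Protocol article*

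**What the plan says.** The protocol article describes a single-group before-and-after study. Three places bear on this point.

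- **Data analysis.** Pre- and post-intervention variables are to be analysed with the paired t-test for means, or by "comparing proportions using the McNemar test".
- **Phase III.** There are two follow-up readings: "Data collection will be done at the end of the 8th and 16th weeks".
- **Methods and analysis (sample size).** The starting figure is that "the proportion of students reporting moderate-to-severe back pain as measured on a VAS scale was 71.6" per cent in the earlier study. The calculation continues: "Assuming that the intervention will cause a 15% reduction in this proportion" "with a 95% confidence interval and 90% power", and "assuming a 20% dropout rate, the calculated sample size is 270 students". For representativeness and subgroup analyses, "this sample size will be doubled to include 540 students".

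The article does not say why students might drop out, or whether dropout is expected to relate to pain.

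**The concern.** McNemar and the paired t-test both work on within-student pairs. A student seen at baseline and week 8 but absent at week 16 adds nothing to the baseline-to-week-16 result, although the week-8 reading has been collected and says something about where that student was heading.

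The result then describes completers. It describes everyone who started the programme only if loss is unrelated to outcome. That is a strong condition here. SanSKAR asks for Surya Namaskars on at least 5 days a week for 16 weeks, no more than 60 minutes of screen time a day, and a diary kept by parents. Students who do not improve or do not comply could plausibly leave more often. The within-student change is the whole effect estimate, so any selection among those who stay enters it directly.

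**Working it through.** **Inputs from the article.** Baseline proportion with moderate-to-severe pain 71.6%; reduction 15%; 95% confidence; power 90%; dropout 20%; stated size 270, doubled to 540.

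**Assumptions added here.** The article does not say whether 15% is absolute or relative, whether the test is two-sided, or what share of students would change category between visits. I take an absolute reduction (p1 = 0.716, p2 = 0.566, d = 0.15), a two-sided 5% level, and discordance as if the two visits were independent.

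**Step 1: reproduce 270.**

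- Discordance: ψ = p1(1 − p2) + (1 − p1)p2 = 0.716 × 0.434 + 0.284 × 0.566 = 0.3107 + 0.1607 = 0.4715.
- Pairs: n = (1.960 × √ψ + 1.2816 × √(ψ − d²))² / d² = (1.3458 + 0.8587)² / 0.0225 = 216.
- Inflated for dropout: 216 / 0.8 = 270, which is the stated figure.

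A standard two-proportion formula gives 213, and 213 / 0.8 rounds up to 267, also close. A relative 15% reduction (to 60.9%) gives 409 pairs and 512 students by the same McNemar formula, so the absolute reading is the one that fits.

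The stated size is thus consistent with 216 complete pairs divided by 0.8. Dropout enters only as a loss of numbers: 54 of 270 students, or 108 if all 540 started the programme. The percentages below do not depend on which number applies.

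**Step 2: what a completer result could mean for all treated students.** Suppose that completers (80%) show the planned 56.6% at week 16, and that completers and dropouts share the 71.6% baseline. Let q be the unseen week-16 proportion among dropouts (20%). The full-cohort proportion is 0.8 × 0.566 + 0.2 × q = 0.4528 + 0.2q.

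| Dropouts at week 16 | q | Full-cohort proportion | Fall from 71.6% |
|---|---|---|---|
| Same as completers | 56.6% | 56.6% | 15.0 points |
| Unchanged from baseline | 71.6% | 59.6% | 12.0 points |
| All in moderate-to-severe pain (extreme) | 100% | 65.3% | 6.3 points |
| None in moderate-to-severe pain (extreme) | 0% | 45.3% | 26.3 points |

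If dropouts did not change, the completer figure is 15.0 − 12.0 = 3.0 points too high. If dropouts did as well as completers, there is no bias. If they did better, the completer figure is too low. Doubling the enrolment changes none of these rows.

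**The case against.** **This may be only a missing policy.** The best reply is that both tests are standard for paired before-and-after data and do not by themselves fix how missing outcomes are handled; either can be run after imputation. A condensed article commonly leaves the analysis set and missing-data rules to a full protocol or SAP, which is not shown. This stands as far as it goes: the article's silence on missing data is no fault. The point is narrower. The article does state a method for the main comparison. As ordinarily run, that method uses complete pairs and sets aside week-8 readings of students missing at week 16.

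**The direction is not shown.** A reader might infer that the estimate will favour those who stay. The article gives no reasons for dropout. Loss could come from absence, transfer, or students stopping once free of pain, and teachers monitor the programme daily. A bias toward benefit is plausible, no more.

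**The size can be overstated.** A reader might also infer that the reported effect could be more than double the real one. That rests on the 6.3-point bound. It requires every dropout below the threshold at baseline (28.4%) to worsen and none of the others to improve, and it ignores the 26.3-point bound on the other side.

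**The tests do not lose every student with a missed visit.** A student who misses week 8 but attends week 16 stays in the baseline-to-week-16 comparison.

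**A control arm would not be a cure.** Loss that differs between arms biases controlled comparisons too, so the single-group design is the setting of the problem rather than its cause.

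**A mixed model does not settle the matter either.** It assumes that data are missing at random. If students leave because of unseen week-16 pain, it remains biased. That is correct, and is why a sensitivity analysis belongs with it.

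**Conclusion.** The concern holds as a possible bias of unknown direction arising from a stated method, and as a cheap improvement. It does not show that the result will be wrong. In the most natural illustration, with dropouts unchanged from baseline, a completer fall of 15.0 points corresponds to 12.0 points in all treated students. The extremes are 6.3 and 26.3 points, and zero bias is possible.

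These figures rest on the absolute reading of the 15% reduction, on 20% loss at week 16, and on completers and dropouts having the same baseline. They are scenarios, not predictions. What does not depend on them is that enlarging the sample cannot remove selection bias, and that the week-16 paired tests as ordinarily run leave collected week-8 data unused.

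**What to change.** Before outcomes are examined, set the following:

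- **Main analysis.** Include every student who starts SanSKAR. Fit a likelihood-based mixed model with visit (0, 8, 16 weeks) as a factor and random intercepts for student and school. Use a logistic model for moderate-to-severe pain and report the week-16 change as a difference in model-based marginal proportions, so that it stays on the scale of the planned effect. Use a linear model for VAS and SDQ scores. The week-8 reading of a student missing at week 16 then contributes.
- **Not as an equivalent.** Ordinary unweighted GEE should not be offered as interchangeable, because it generally needs dropout to be completely at random.
- **Sensitivity analysis.** Count students missing at week 16 as unchanged from baseline, since the mixed model still assumes missing at random.
- **Supportive.** Keep McNemar and the paired t-test, labelled as completer analyses.

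The cost is slightly more analysis work, including a check that the software used fits the logistic model by likelihood. No new data or visits are needed. The downside is that the reported effect may be smaller than the completer figure.
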